### 2. Objectives and Hypotheses

**Primary Objective:** To determine whether the intervention reduced the cumulative 12-month incidence of T2DM among individuals with prediabetes.

**Secondary Objectives:** To assess the intervention's effect on body weight, BMI, glycemic indices (FPG, 2hPG, HbA1c), lipid profiles, physical activity, diabetes knowledge, and quality of life.

**Hypothesis:** The intervention group had a lower incidence of T2DM and greater improvements in cardiometabolic outcomes than the control group.

### 3. Trial Design and Randomization

A cluster-randomized parallel-group design was used with 8 mosques as units of randomization. Mosques were randomized 1:1 to intervention or control groups using a computer-generated block randomization schedule (block size = 2), stratified by district. The allocation sequence was prepared by an independent statistician. Field staff enrolled participants and assigned them post-randomization.

### 4. Sample Size

Cluster sizes were assumed to be equal in sample size calculation; actual variability was minor (range 92–110).

Calculated to detect a 7% absolute reduction in diabetes incidence (control assumed 12% incidence), with 80% power, 5% significance, and design effect (ICC=0.041 from pilot data).

Final sample: 799 participants (396 intervention, 403 control) after exclusions (25 excluded due to [specify reasons: e.g., baseline diabetes, withdrawal]).

Achieved power: 82% post-hoc (given observed ICC=0.039).

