#### **Key Parameters for Sample Size Calculation:**

1. Primary Outcome: A 50% reduction in T2DM incidence in the intervention group compared to the control group.

2. Power: 80% power to detect the effect.
3. Significance Level: 5% ( $\alpha = 0.05$ ).
4. Intraclass Correlation Coefficient (ICC): 0.05 to account for clustering within mosques.
5. Dropout Rate: 50% to account for potential loss to follow-up.

The sample size calculation used the following formula for cluster-randomized trials:

$$n = 2 \cdot (Z_{\alpha/2} + Z_{\beta})^2 \cdot p \cdot (1-p) \cdot DE / (p_1 - p_2)^2$$

Where:

- $Z_{\alpha/2} = 1.96$  (for a 5% significance level).
- $Z_{\beta} = 0.84$  (for 80% power).
- $p$  = overall event rate (T2DM incidence in the control group).
- $p_1$  = event rate in the control group.
- $p_2$  = event rate in the intervention group (50% reduction).
- $DE$  = design effect, calculated as  $1 + (n-1) \cdot \rho$ , where  $\rho = 0.05$  (ICC).

*Assumptions:*

- The 5-year cumulative incidence of T2DM in Bangladesh was 16.4 per 1,000 person-years [34].
- A 50% reduction in T2DM incidence in the intervention group was assumed, based on previous trials.
- The design effect (DE) was calculated as 6.1, accounting for clustering within mosques.

*Calculation:*

1. Number of Participants per Arm:
  - Based on the formula and assumptions, 412 participants per arm were required to detect a 50% reduction in T2DM incidence with 80% power and a 5% significance level.
2. Total Sample Size:
  - To account for a 50% loss to follow-up, the total sample size was increased to 824 participants (412 in the intervention group and 412 in the control group).
3. Number of Clusters:
  - Participants were recruited from eight mosques, with approximately 103 participants per mosque.

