## **9. Statistical Software**

All analyses were performed using STATA version 17.0 (StataCorp, College Station, TX, USA). MI via 'mi estimate', GEE via 'xtgee'. A two-sided p-value <0.05 was considered statistically significant.

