## **10. Deviations from the Protocol**

- No changes were made to the primary or secondary outcome definitions.
- Per-protocol and imputation-based sensitivity analyses were added during analysis to enhance robustness.

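### SAP section 4 restates the planning basis for the 824 participants with a larger effect, smaller ICC and higher control rate than the protocol, unlisted as deviations, and neither set of inputs supports the stated power

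*Combined protocol and SAP*

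**What the plan says.** **Protocol section 10.6** sizes the trial on a relative effect: "A 50% reduction in T2DM incidence in the intervention group was assumed, based on previous trials". For clustering it gives "Intraclass Correlation Coefficient (ICC): 0.05 to account for clustering within mosques", with a design effect of 6.1. The event rate is 16.4 per 1,000 person-years and the dropout allowance is 50%. The result is 412 per arm, 824 in total, in eight mosques of about 103. The same section cites a 58% reduction from two landmark lifestyle trials as the background to choosing 50%.

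**SAP section 4** says "Calculated to detect a 7% absolute reduction in diabetes incidence (control assumed 12% incidence), with 80% power" and "5% significance, and design effect (ICC=0.041 from pilot data". It then reports "Final sample: 799 participants (396 intervention, 403 control) after exclusions", with 25 excluded, and "Achieved power: 82% post-hoc (given observed ICC=0.039". SAP section 9 sets the test: "A two-sided p-value <0.05 was considered statistically significant".

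The SAP is labelled retrospective, is dated 20 August 2023, and states that it was written after data collection and before the primary analysis. **SAP section 10** says the outcome definitions did not change and records one addition: "Per-protocol and imputation-based sensitivity analyses were added during analysis to enhance robustness". It does not mention sample-size inputs.

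**The concern.** Both documents describe the same sample, since 799 + 25 = 824, yet they attach different planning assumptions to it. Someone reading only the SAP would take 12% vs 5% with ICC 0.041 as the basis on which the trial was sized. The protocol contains neither figure, and it contains no 12% control rate. The only pilot work it describes is pretesting of the questionnaire, so the source of a pilot ICC is not shown.

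What is at stake is how the result is read. A stated power of 80% or 82% tells readers that the trial could reliably detect the target effect. If the target is not the protocol's and the power does not follow from the inputs, a null result would look more conclusive than it is, and the record of what was prespecified is blurred.

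**Working it through.** **Inputs.** SAP: control 12%, intervention 12% − 7% = 5%, ICC 0.041 planned and 0.039 observed, 799 analysed (about 399.5 per arm, 99.9 per mosque), two-sided 5%. Protocol: 50% reduction, ICC 0.05, 16.4 per 1,000 person-years (taken as 1.64% over one year, so 0.82% under intervention), 412 per arm, 103 per mosque.

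**Relative effects.** SAP: 7/12 = 58.3%. Protocol: 50%.

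**Method.** Design effect DE = 1 + (m − 1) × ICC. Effective n per arm = n/DE. SE = √{[p1(1 − p1) + p2(1 − p2)]/n_eff}. Normal power = Φ(|p1 − p2|/SE − 1.96). The t version uses the non-central t with 6 df (8 mosques − 2 arms).

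**SAP's 80%.** DE = 1 + 98.9 × 0.041 = 5.05, so n_eff = 399.5/5.05 = 79. SE = √[(0.1056 + 0.0475)/79] = 0.0440, and 0.07/0.0440 = 1.59. Power is Φ(−0.37) = 36%, or 27% by t.

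**SAP's 82%.** At ICC 0.039, DE = 4.86, n_eff = 82, SE = 0.0431 and the ratio is 1.62. Power is 37%, or 28% by t. Reaching 82% by the normal method would need an ICC of about 0.005. Ignoring clustering altogether gives 95%, so the 80% and 82% match neither calculation.

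**Required n for the SAP's inputs.** 7.84 × (0.1056 + 0.0475)/0.07² = 245 per arm before clustering. At m = 103, DE = 1 + 102 × 0.041 = 5.18, and 245 × 5.18 ≈ 1,270 per arm.

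**Protocol's 412.** The printed formula is 2 × 7.84 × p(1 − p) × 6.1/(0.0164 − 0.0082)². The text calls p both the overall rate and the control rate, so both were tried:
- p = 0.0123 (mean of the two arms): about 17,300 per arm
- p = 0.0164 (control): about 22,900 per arm

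Both are before dropout. The protocol also gives 412 per arm both before and after its 50% dropout inflation.

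**Power by effect and ICC** (799 analysed in eight mosques):

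| Comparison | ICC | Normal | t, 6 df |
|---|---|---|---|
| 12% vs 5% (SAP) | 0.041 | 36% | 27% |
| 12% vs 5% (SAP) | 0.039 | 37% | 28% |
| 12% vs 6% (assumed hybrid) | 0.041 | 26% | 20% |
| 12% vs 6% (assumed hybrid) | 0.05 | 23% | 18% |
| 1.64% vs 0.82% (protocol) | 0.05 | about 6% | about 7% |

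Using 412 per arm, or a pooled variance in the normal calculation, moves these figures by less than one percentage point.

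The hybrid row applies the protocol's 50% reduction to the SAP's 12% control rate. That pairing is an assumption, because neither document states 12% vs 6%. Before clustering it needs 7.84 × (0.1056 + 0.0564)/0.06² = 353 per arm, 44% more than 245.

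**The case against.** **Planning inputs do not change the analysis.** This is correct. The estimate, interval and test in SAP section 7.2 are unaffected, so this is an error of reporting and transparency.

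**A 12% control rate may suit people with prediabetes better than a rate quoted for Bangladesh as a whole.** It may, but the SAP gives no source for it and does not say that it replaces the protocol's figure.

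Three stronger readings are tempting, and the documents do not support them:

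- *The sponsor chose the more favourable values after seeing the data.* The documents do not show when 12%, 7 points or 0.041 were chosen. The SAP attributes the ICC to pilot data, and its declaration places it before the primary analysis. What they do show is that the values first appear in a SAP written after data collection.
- *The 824 was properly derived from the protocol's inputs and the SAP then rewrote a sound calculation.* The protocol's inputs do not yield 412 per arm by its own formula. It can only be said that the protocol states 824 alongside those inputs.
- *Moving from the SAP's effect to the protocol's costs 7 to 10 points, so true power is 70% to 73%.* With 12% held fixed, a gap of about that size does arise (36% to 26%, or 27% to 20% by t, at ICC 0.041). But it starts from about 36%, not 80%, and it rests on the hybrid 12% vs 6%. Subtracting it from 80% would treat as valid a figure that does not hold even at 12% vs 5%.

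**Conclusion.** The point holds as an undisclosed contradiction between the two planning bases, together with power figures that neither basis supports. Three inputs differ: effect (58% vs 50% reduction), ICC (0.041 vs 0.05) and control rate (12% vs 16.4 per 1,000 person-years). All three SAP values raise power, and none is listed as a deviation.

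The size of the power error depends little on method: at 12% vs 5%, the design gives roughly 27% to 37% where the SAP states 80% and 82%. This rests on equal mosque sizes, which the SAP also assumes, and on the usual design effect.

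The figures for the protocol's effect are less firm. The 18% to 26% range depends on borrowing the SAP's 12% rate. The 6% depends on reading the protocol's incidence as a one-year risk of 1.64%; the protocol labels that number as a five-year cumulative incidence but gives it in person-years.

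**What to change.** In SAP section 4:

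1. Report the protocol's stated inputs (50% reduction, ICC 0.05, 16.4 per 1,000 person-years, 50% dropout) as the planning basis, and say that they do not reproduce 412 per arm.
2. Remove the statement that the sample size was calculated from 12% vs 5% and ICC 0.041. Label these as values that first appear in the retrospective SAP, and give the source of the pilot ICC and of the 12%.
3. Replace the 80% with power recomputed for eight clusters, at the SAP's effect and at the protocol's, stating the control rate used for each. Delete the 82% or replace it on the same basis.

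In SAP section 10, list the changed effect size, ICC and control rate.

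The cost is a rewritten paragraph and three lines under deviations. No new data, enrolment or change to the primary analysis is needed. The price is a published power far below 80%, which the discussion of the results would have to acknowledge.

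### Four mosques per arm do not give the 80% power that SAP section 4 claims for 12% vs 5%: its own inputs give about 36% (normal) or 27% (t, 6 df), and the 82% achieved power has no stated effect size behind it

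*Combined protocol and SAP*

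**What the plan says.** SAP section 4 gives the planning basis: "Calculated to detect a 7% absolute reduction in diabetes incidence (control assumed 12% incidence"). The target there is 80% power at the 5% level, and clustering enters through a "design effect (ICC=0.041 from pilot data"). The section treats mosques as equal in size, gives an actual range of 92 to 110, and reports a final sample of 799 (396 intervention, 403 control). It then states "Achieved power: 82% post-hoc (given observed ICC=0.039"). It gives no design-effect value, formula or degrees of freedom, and no effect size for the 82%.

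SAP section 3 fixes the number of clusters: "A cluster-randomized parallel-group design was used with 8 mosques as units of randomization", allocated 1:1. SAP section 9 fixes the test level: "A two-sided p-value <0.05 was considered statistically significant".

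Protocol 10.6 uses other inputs: an incidence of 16.4 per 1,000 person-years, a 50% relative reduction, a design effect of 6.1 and "Intraclass Correlation Coefficient (ICC): 0.05 to account for clustering within mosques". It arrives at 412 per arm.

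**The concern.** In a cluster trial the number of clusters limits the information, and eight is very few. An ICC near 0.04 with about 100 people per mosque divides the effective sample size by roughly five. About 400 people per arm then carry the information of about 80, and 80 per arm is not enough to separate 12% from 5% with 80% power.

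The figures describe how well the design could answer the primary question. A reader who accepts 80% or 82% could take a null result as good evidence of no worthwhile effect, or a positive result as coming from a well-powered trial. Neither reading would be justified at power near 30%. The SAP declares that it reflects the analysis used in the manuscript, so the figures could be carried into the publication.

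**Working it through.** **Inputs.** Control incidence 0.12, reduction 0.07, hence 0.05 under intervention (SAP 4). Two-sided 0.05 (SAP 9). 80% power (SAP 4). Four mosques per arm (SAP 3: 8 mosques, 1:1). Average per arm 799/2 = 399.5, so m = 399.5/4 = 99.9 per mosque. ICC 0.041 planned and 0.039 observed (SAP 4); 0.05 in protocol 10.6. No dropout is applied, because loss to follow-up only lowers power.

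**1. Attempt to reproduce the planned 80%.**
- Without clustering: n = (1.96 + 0.84)² × (0.12×0.88 + 0.05×0.95) / 0.07² = 7.84 × 0.1531 / 0.0049 = 245 per arm.
- Design effect: 1 + (99.9 − 1) × 0.041 = 5.05.
- With clustering: 245 × 5.05 ≈ 1,240 per arm, which is 12.4 mosques of 100 and therefore 13 per arm (14 if the t correction below is used). The trial had 4 mosques and about 400 people per arm.

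**2. Power that the design gives.** Effective n = 399.5 / design effect. Standardised difference d = 0.07 / √(0.1531 / effective n). Normal power is Φ(d − 1.96). The t figure uses a noncentral t with 2×4 − 2 = 6 df.

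| ICC | Design effect | Effective n per arm | d | Power, normal | Power, t (6 df) |
|---|---|---|---|---|---|
| 0.039 | 4.86 | 82.3 | 1.62 | 36.8% | 27.8% |
| 0.041 | 5.05 | 79.0 | 1.59 | 35.6% | 26.9% |
| 0.05 | 5.94 | 67.2 | 1.47 | 31.1% | 23.6% |

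**3. Ceiling.** As mosque size grows without limit, effective n per arm tends to 4/ICC. At ICC 0.041 this is 4/0.041 = 97.6, so d = 1.77 and power tops out at 42% (normal) or 32% (t, 6 df). Recruiting more people from the same mosques could not have reached 80%.

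**4. Attempt to reproduce the 82%.** For 12% vs 5% at ICC 0.039, power is 36.8% or 27.8% (table). Moving the ICC from 0.041 to 0.039 adds only about one point. Ignoring clustering altogether gives d = 3.58 and 94.7% by the normal approximation, so that does not produce 82% either. For this effect, 82% would need an ICC of about 0.0055 (normal) or 0.0007 (t, 6 df).

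**5. Other routes tried for 12% vs 5%.** A one-sided test gives 47–49% (normal), an arcsine comparison 36–38%, a log-rank events formula with events divided by the design effect 39–40%, and the protocol's formula 27–54% depending on the value of p. Using 412 per arm gives 35–37%. Mistaking the total of 799 for a per-arm figure gives at most 63%. None reaches 80%.

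**6. What is detectable.** With 12% control incidence and ICC 0.039, an intervention incidence of 1.3% gives 80.5% by the normal approximation but 65% on 6 df. On 6 df, even zero incidence gives 79.6%.

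**The case against.** The strongest reply concerns the 82%. A reader might infer from the table that this figure is false. The documents do not support that, because SAP section 4 ties it only to the observed ICC. It does not say whether it uses the assumed 12% vs 5% or the observed rates, and no observed rates are reported. Taking assumed rates to show the range, at ICC 0.039 the normal approximation gives 82% at 15% vs 2.6%, 20% vs 5.4% or 25% vs 8.6%; on 6 df it takes about 20% vs 3.3%. These are large effects, but the documents do not exclude them. This part of the reply stands. It does not rescue the figure as a statement about the design: power computed at the observed effect mostly restates the p-value.

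Second, the t figures are not the power of the specified analysis, which is a log-rank test and a Cox model with mosque-level shared frailty (SAP 7.2). District stratification might also remove some between-mosque variance. Both points are fair. The t figures are a small-cluster caution and should be labelled as such, separately from the normal figures. But SAP section 4 credits no gain from stratification or adjustment, and the normal figure alone is less than half of 80%.

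Third, the SAP postdates data collection, so no design decision turns on these figures and no estimate, interval or test changes. That is true, and it is why the remedy is confined to wording.

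Fourth, section 10 of the SAP does not assert that the sample-size inputs were unchanged; it speaks of outcome definitions and added analyses. A reader might infer deliberate concealment. The documents show only an omission.

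**Conclusion.** The 80% planning statement is wrong on the SAP's own inputs: power for 12% vs 5% is about 36% (normal) or 27% (t, 6 df) at ICC 0.041, a shortfall of about 44 or 53 points. About three times the available participants would have been needed, spread over at least 13 mosques per arm.

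The 82% is unsupported. It does not follow for the stated effect (37% normal, 28% t with 6 df at ICC 0.039), and no other effect is given. If it rests on observed rates, it says nothing about the design.

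It would also be too strong to say simply that near-elimination of diabetes was detectable with 80% power. That holds only by the normal approximation, with 12% control incidence; on 6 df even zero incidence falls just short.

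These conclusions assume four near-equal mosques per arm, no loss to follow-up, no precision gain from stratification or covariates, and the ICCs as stated. They concern the claimed power, not the validity of the primary analysis.

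A secondary reporting point is that the SAP's inputs (12%, 7 points, which is 7/12 = 58% relative, and ICC 0.041) differ from those in protocol 10.6, and SAP section 10 does not list the change.

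**What to change.** In SAP section 4, and wherever the figures are repeated in the manuscript, delete the 80% and 82% statements. Replace them with:

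> With 4 mosques per arm and about 100 participants each, power for 12% vs 5% (two-sided 0.05) is about 31–37% by normal approximation, or 24–28% with a small-cluster t correction (6 df), for ICC 0.05 to 0.039.

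If a detectable effect is wanted, give its conditions: by normal approximation, with 12% control incidence and ICC 0.039, 80% power needs an intervention incidence of about 1.3%; on 6 df even zero incidence gives just under 80%. Otherwise leave it out.

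Drop post-hoc power and interpret the primary result by its cluster-adjusted confidence interval.

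In SAP section 10, list the change from the protocol's inputs (16.4 per 1,000 person-years, 50% reduction, ICC 0.05) to the SAP's (12%, 7 points, ICC 0.041), with the reason.

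The cost is a few sentences and a less favourable stated power. It needs no new data, participants or analyses.

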### 5. Analysis Populations

- **Intention-to-Treat (ITT):** All randomized participants analyzed per original allocation.
- **Modified ITT:** Excludes only participants with no post-baseline data (n=10).
- **Per-Protocol (PP):** Intervention group restricted to participants with  $\geq 75\%$  attendance (verified by mosque sign-in sheets).

### 6. Handling of Missing Data

**Primary:** Complete-case analysis. Sensitivity analyses:

- **Multiple imputation (MI):** 10 imputations using chained equations (predictors: age, sex, baseline HbA1c, mosque cluster).
- **Best-case/Worst-case scenarios:** Best-case assumes dropouts had no diabetes; worst-case assumes all developed diabetes.
- **Pattern-mixture models** to test missing-not-at-random (MNAR) assumptions.

**Report:** Flow diagram with missing data by arm and reasons.

No formal adjustment for multiplicity was applied; secondary outcome results should be interpreted as exploratory.

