### 10.7. Randomization and Masking

Participants will be randomized after the project research team determined that they:

1. Will demonstrate a satisfactory interest in joining lifestyle intervention during the run-in.
2. Will express willingness to continue in the trial.
3. Will meet all inclusion/exclusion criteria.
4. Will provide all baseline data.

After exclusions, 824 participants will be allocated at random in a 1:1 ratio to an intensive lifestyle intervention to promote increased physical activity and dietary modification or to minimal lifestyle advice to the control group. Randomization lists will be generated and supplied by the coordinating center, and staff who will perform the baseline measurements will have no access to the randomization lists. Neither staff delivering the intervention nor participants will be masked to the study arm.

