## 12. Data analysis

A data safety officer will monitor the study. The primary and secondary outcomes will be analysed using the intention-to-treat approach. Differences in baseline characteristics and clinical outcomes between the two groups will be evaluated using two-sample t-tests for continuous variables and chi-square tests for categorical variables.

For the primary outcome, the cumulative incidence of T2DM will be compared between the two groups using a log-rank test with random effects for intercept to account for pre-post correlations within participants. The intervention effect will be assessed at each time point. For secondary outcomes, which will be continuous variables, repeated-measure linear mixed models will be used to assess differences between groups over time.

The incidence rate of diabetes will be calculated by dividing the number of new diabetes cases by the total person-time of follow-up, expressed per 1,000 person-years. This method will account for participants with differing lengths of follow-up, including those who drop out or are lost to follow-up. Incidence rates will be

reported as events per 1,000 person-years, along with 95% confidence intervals (CIs), to provide a measure of precision and enable comparisons between groups.

The cumulative incidence of T2DM over the 12-month follow-up period will be estimated using Kaplan-Meier survival analysis. Differences between the survival curves will be tested using the log-rank test to determine statistical significance. To quantify the intervention effect, hazard ratios (HRs) with 95% CIs will be calculated using a Cox proportional hazards regression model, which will adjust for the time to diabetes development. Participants who do not develop T2DM or are lost to follow-up will be censored at the time of their last follow-up, ensuring accurate risk estimation.

For intervention measures, chi-square tests will be used to compare event rates between the intervention and control groups. Absolute risk reduction (ARR) and relative risk reduction (RRR) will be calculated, with risk ratios used to quantify the relative difference in event rates between the two groups. Confidence intervals for ARR and RRR will be computed to estimate the precision of the findings. The number needed to treat (NNT) to prevent one case of T2DM will be determined to evaluate the practical impact of the intervention.

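### SAP 6 makes complete-case the primary approach, against the trial's intention-to-treat commitment and censoring rule, and the 25 exclusions behind the sample of 799 are unexplained

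*Combined protocol and SAP*

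**What the plan says.** **Commitment.** Protocol section 12: "The primary and secondary outcomes will be analysed using the intention-to-treat approach". SAP 5 defines the ITT set as "All randomized participants analyzed per original allocation".

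**Loss to follow-up.** Protocol section 12, for the Kaplan-Meier and Cox analysis: "Participants who do not develop T2DM or are lost to follow-up will be censored at the time of their last follow-up".

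**Primary handling of missing data.** SAP 6 gives the primary approach and opens its list of alternatives in one line: "Complete-case analysis. Sensitivity analyses". The alternatives are multiple imputation, best-case/worst-case scenarios and pattern-mixture models. The same section asks for a flow diagram of missing data by arm, with reasons.

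**Counts.** Protocol section 10.7: "After exclusions, 824 participants will be allocated at random in a 1:1 ratio". SAP 4: "Final sample: 799 participants (396 intervention, 403 control) after exclusions (25 excluded due to [specify reasons: e.g., baseline diabetes, withdrawal"; the bracket is a template field that was never completed. SAP 5 on modified ITT: "Excludes only participants with no post-baseline data (n=10".

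**What is not said.** SAP 7.2 specifies Kaplan-Meier, log-rank and a shared-frailty Cox model but names no analysis population and no censoring rule. SAP 10 records that per-protocol and imputation analyses were added during analysis. It does not mention complete-case handling.

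**The concern.** An analysis of complete cases within a sample already reduced by 25 people is not, on its face, an analysis of everyone randomised. The protocol keeps people who are lost in the analysis up to their last follow-up, whereas a complete-case rule, as usually understood, removes them. The SAP puts the second rule in the primary position without saying how it fits with the first.

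The stake is the primary comparison. Participants and those delivering the intervention knew the allocation, so who leaves, and why, may differ by arm. Removing withdrawals after the mosques were allocated would forfeit the protection that randomisation gives. A complete-case rule requiring a 12-month OGTT would also drop a person found to have T2DM at the 4-month OGTT who then left, although that person is already an incident case. Because SAP 7.2 names no population, a reader cannot tell who is in the primary hazard ratio.

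**Working it through.** **1. The SAP's own count.** 396 + 403 = 799, and 824 − 25 = 799. So 799 reproduces exactly if 824 people entered, which is the protocol's target. The 25 are 25/824 = 3.0%.

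**2. The 25 against the 10.** There are two readings of modified ITT:
- taken from 824: 824 − 10 = 814, which is more than the final sample of 799;
- taken from 799: 799 − 10 = 789, so the base of 799 already omits 25 people.

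The second reading agrees with the ITT definition only if the 25 never properly belonged to the trial, for example because all had T2DM at the baseline OGTT, which the protocol's run-in paragraph (section 11) excludes. The SAP does not say so, and its placeholder gives withdrawal as another possible reason.

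**3. Timing.** The protocol's 824 is already a number after exclusions, and baseline T2DM is to be removed at run-in. SAP 3 has participants assigned once the mosques had been randomised. Removal after allocation is therefore the natural reading, but it is not stated.

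**4. Split by arm (assumption).** If 412 per arm were enrolled, as planned in protocol 10.6:
- intervention: 412 − 396 = 16 excluded (16/412 = 3.9%);
- control: 412 − 403 = 9 excluded (9/412 = 2.2%).

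**5. How much 25 people could matter (illustration).** The documents contain no outcome data, so the SAP 4 planning rates stand in: 12% in control and 12 − 7 = 5% in intervention. Cases among the 799 are then 0.05 × 396 ≈ 20 and 0.12 × 403 ≈ 48. Adding the 16 and 9 back:

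| Assumed T2DM among the excluded | Intervention | Control | Difference (points) | RR |
|---|---|---|---|---|
| Left out | 20/396 = 5.1% | 48/403 = 11.9% | 6.9 | 0.42 |
| None | 20/412 = 4.9% | 48/412 = 11.7% | 6.8 | 0.42 |
| All 25 | 36/412 = 8.7% | 57/412 = 13.8% | 5.1 | 0.63 |
| Only the 16 intervention | 36/412 = 8.7% | 48/412 = 11.7% | 2.9 | 0.75 |
| Only the 9 control | 20/412 = 4.9% | 57/412 = 13.8% | 9.0 | 0.35 |

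A Pearson chi-square that ignores clustering gives p = 0.0005 with the 25 left out and p = 0.17 in the least favourable row. These p-values show sensitivity only; allowing for clustering would weaken the evidence in both.

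The SAP's best-case and worst-case scenarios, as written, make the same assumption for dropouts in both arms. They correspond to the None and All rows (6.8 and 5.1 points). The two ends of the range, 2.9 and 9.0, arise only when the assumption differs by arm.

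**The case against.** The strongest reply is that the plan can be read as coherent. SAP 6 never says that a complete case needs a 12-month OGTT. Under Kaplan-Meier and Cox, a 4-month diagnosis is an event and a person seen only at 4 months contributes censored time. SAP 10 does not revoke the protocol's censoring rule. Complete-case could then mean dropping only those with no follow-up at all, about the 10 in modified ITT. If all 25 were baseline-diabetes exclusions, 799 eligible and 789 in modified ITT fit together. The SAP also plans three kinds of sensitivity analysis and a flow diagram, and outcome assessors were blinded.

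Much of this stands, and it rules out several stronger inferences:
- **That known 4-month cases are discarded.** This depends on a definition of complete-case that the SAP does not give.
- **That the counts cannot be reconciled.** They can, under one explanation of the 25 that the SAP does not state.
- **That half of each arm is lost.** The 50% in protocol 10.6 is a planning allowance. The SAP, written after data collection, reports 10 with no post-baseline data and does not say how many missed only the 12-month visit.
- **That the effect is overstated.** The range runs both ways. Anyone among the 25 with baseline diabetes should not be counted as an incident case at all.

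The reply does not remove the conflict. A benign reading is possible but not written down. The sensitivity analyses leave the primary result on the complete-case rule, and blinded assessment does not protect against selective exclusion.

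**Conclusion.** The point holds as a conflict in the stated rules together with an undefined primary population. Complete-case as the primary approach contradicts the ITT commitment and the protocol's censoring rule, and SAP 10 does not disclose it. The reasons and timing of the 25 exclusions are missing, and the 25 are not reconciled with the 10.

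Whether the primary result departs from ITT is conditional. It does if any of the 25 were withdrawals after mosque allocation, or if complete-case is applied as requiring a 12-month OGTT. In either case bias is possible, but the documents fix neither its size nor its direction. The range of 2.9 to 9.0 points around 6.9 is an illustration. It rests on 412 enrolled per arm, on planning rates in place of results, and on extreme assumptions about the 25. If all 25 had T2DM at baseline, the illustration does not apply and the concern about them largely falls away. The missing-data rule would still need correction.

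**What to change.** 1. **Primary set.** All participants enrolled at the 8 mosques, analysed as allocated. Exclude only those with T2DM at the baseline OGTT and those who used the right in protocol section 14 to have their data omitted. Count both by arm. Name this set in SAP 7.2.
2. **Primary handling.** In the Kaplan-Meier/Cox analysis, count T2DM at the 4-month OGTT as an event whether or not the 12-month visit took place. Censor others who are lost at their last OGTT, as in the protocol.
3. **Sensitivity.** Move complete-case here, beside the imputation, best-case/worst-case and pattern-mixture analyses already planned, and define it. Add an extreme case in which the assumption differs by arm. This matters because people with no post-baseline OGTT stay in the primary set but contribute no follow-up time, so only these analyses show their possible influence.
4. **Counts.** Replace the placeholder in SAP 4 with the reasons and timing of the 25 by arm and mosque, and reconcile 824 and 799 with the 10.
5. **Disclosure.** Record the change of missing-data approach in SAP 10.

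The cost is SAP wording and a re-run. The re-run needs no new data collection, but whether post-baseline results are held for any of the 25 is not stated and should be checked first.
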